### Eligibility criteria {10}

A patient may be included in the clinical trial if they meet all of the following criteria:The participant is a person with a histologically proven diagnosis of glioblastoma (GBM) according to WHO 2016.The participants are male or female and aged 18 years or older.Performance status (PS) according to ECOG (Eastern Cooperative Oncology Group) 0–2.Healed operation wound.Postoperative MR up to 72 h.Indication for adjuvant chemoradiotherapy.The participants must express his/her informed consent and sign the form before the screening period.Rapid early progression was detected.The participants must achieve the following values of laboratory parameters in the peripheral blood during the screening period:neutrophils (total count) ≥ 1500/mm.3platelets (total count) ≥ 100,000/mm.3hemoglobin ≥ 9.0 g/dLserum creatinine ≤ 1.5 × of upper limit of normal (ULN)total bilirubin ≤ 1.5 × ULN, unless documented Gilbert's syndrome, for which bilirubin ≤ 3 × ULN is permitted AST/ALT ≤ 3 × ULN

The exclusion criteria were as follows:Prior brain surgery.Prior brain radiotherapy.The history of active/currently treated cancer (solid tumor) was as follows: nonmelanoma skin cancer, in situ bladder carcinoma, in situ gastric cancer, in situ colorectal carcinoma, in situ cervical carcinoma, and in situ breast cancer.Any systemic disease or health condition that might pose a risk for anticancer therapy and imaging techniques (MRI, MET PET).Patients must not have substance abuse disorders that would interfere with cooperation with the requirements of the trial.Patients must not have any evidence of ongoing (active) infection (HIV, hepatitis A, B, C).Pregnant and/or breastfeeding women.Patients who disagreed and refused to sign an informed consent form.

### Intervention description {11a}

The intervention is the radiopharmaceutical application performing ^11^C-methionine PET examination. The activity of the ^11^C-methionine applied for each patient will be 300 MBq (± 50 MBq) of ^11^C-methionine. The preparation of ^11^C-methionine for a specific patient is provided by a lab worker only be performed with written consent. ^11^C-MET will be sufficiently hydrated, meaning that they have not consumed any food for at least 4 h prior to application. To obtain the best quality images and to reduce radiation exposure to the bladder, the patient will be asked to drink plenty of fluids and void before the PET scan. After a PET scan, the bladder should be emptied as often as possible. If patient sedation is needed, it will be started approximately 20–60 min before the start of the examination. The application of the radiopharmaceutical will be carried out after ensuring venous access with an intravenous cannula. Finish the application by rinsing with 20 ml of physiological solution. The patient will be monitored for 2 h after the application of the radiopharmaceutical due to the possibility of a hypersensitivity reaction.

### Criteria for discontinuing or modifying allocated interventions {11b}

The clinical trial will be interrupted or prematurely terminated for the following reasons:In the case of serious adverse events, the resulting benefit-risk ratio is unacceptable.In the event that other comparable clinical evaluations reveal an unacceptable level of risk for the evaluation subjects. The sponsor reserves the right to interrupt or prematurely end the clinical trial at the centre in the event that:(i)the safety of the subjects would be significantly compromised,(ii)sufficient recruitment would not be achieved,(iii)there would be repeated deviations from the protocol on the part of the investigating centre.

### Strategies to improve adherence to interventions {11c}

Training before initialization ensures compliance during the whole study. If there are doubts, a chief investigator is designated to address them.

### Relevant concomitant care permitted or prohibited during the trial {11d}

The modification consists of changing the irradiation plan. Two chemoradiotherapy regimens of concomitant chemoradiotherapy with temozolomide are permissible at the discretion of the attending physician [31–33]:

#### Regime according to Stupp:

RT 60 Gy/30 fr. each 2.0 Gy (6 weeks, Mon-Fri) + temozolomide 75 mg/m^2^ D1-42 including weekends, then adjuvant temozolomide 150–200 mg/m^2^ D1-5, 28-day interval, six cycles with the possibility of extension to a total of 12 cycles (if no more than low-grade adverse effects occur and if a benefit is demonstrated) or until progression or toxicity.

#### Perry's regimen

RT 40.05 Gy/15 fr. each 2.67 Gy (3 weeks, Mon-Fri) + temozolomide 75 mg/m^2^ D1-21 including weekends then adjuvant temozolomide 150–200 mg/m^2^ D1-5, interval 28 days, max. 12 cycles or until progression or toxicity.

The choice of regimen is at the discretion of the attending physician. In general, the Perry regimen is used for frail and elderly patients, and these patients would probably not be able to handle the classic long Stupp regimen. It is a modified Stupp regimen, where there is a shorter (3-week) concomitant CHT/RT with 40.05 Gy instead of 6 weeks with 60 Gy, followed by classical adjuvant 150–200 mg/m^2^, but up to 12 cycles of temozolomide.

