### Sample size {14}

A historical retrospective cohort included 44 patients with REP who were indicated for adjuvant chemoradiotherapy (Arm Ahist). The median PFS in this cohort was 4.9 months. Assuming that the time distribution in the Experimental Arm follows a proportional hazard model, a significance level of 5%, and a power of 80%, 65 events are needed to detect a hazard ratio of 1.65 (i.e., median PFS in the Experimental Arm of 8 months). With an assumed recruitment of 38 months and a follow-up duration of six months, 67 patients are needed based on the historical cohort. With the expected screening failure rate of 5% and a dropout rate of 5%, approximately 75 patients with confirmed REP should be enrolled.

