## Statistical methods

### Statistical methods for primary and secondary outcomes {20a}

All data will be described for each arm separately and for the entire group of patients. The appropriate descriptive statistics will be used, i.e., counts and percentages for categorical characteristics and median and interquartile range (IQR) or mean and standard deviation (SD) for continuous characteristics. Depending on the data type, common statistical tests such as Fisher's exact test or chi-square test for comparing categorical variables and nonparametric Mann‒Whitney test or Kruskal‒Wallis test for comparing continuous variables or their parametric alternatives if the assumption of data normality is met will be used for comparison of patient characteristics between arms.

The survival parameters that will be considered are progression-free survival (PFS) and overall survival (OS). PFS is considered the time from the start of radiotherapy to the occurrence of progression or death. OS is considered the time from surgery to death (in relation to GBM). The Kaplan‒Meier method will be used to estimate the probability of survival. Survival comparisons between groups will be made using the log-rank or Gehan-Wilcoxon test. The Cox proportional hazards model will be used to calculate the hazard ratio in univariable and multivariable analyses.

All statistical tests and confidence intervals will be calculated at a significance level of 5%.

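### Regimen follows frailty and age at the physician's choice, yet the primary PFS comparison with the historical cohort is unadjusted and sections {20a} and {20b} disagree on adjustment, so a case-mix difference can mimic or hide a PET effect

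*Protocol article*

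**What the plan says.** Section {11d} describes what the trial changes: "The modification consists of changing the irradiation plan". The same section adds: "Two chemoradiotherapy regimens of concomitant chemoradiotherapy with temozolomide are permissible at the discretion of the attending physician". The two courses are 60 Gy in 30 fractions over six weeks and 40.05 Gy in 15 fractions over three weeks. On who receives which, the Perry subsection says: "The choice of regimen is at the discretion of the attending physician. In general, the Perry regimen is used for frail and elderly patients".

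The comparator is historical (sections {6b} and {8}), and {8} calls the framework confirmatory. Section {14} describes it so: "A historical retrospective cohort included 44 patients with REP who were indicated for adjuvant chemoradiotherapy (Arm Ahist", with a median PFS of 4.9 months. The article gives no regimen split for that cohort. Section {12} compares PFS between the arms as a whole.

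For the test, section {20a} states: "Survival comparisons between groups will be made using the log-rank or Gehan-Wilcoxon test". The next sentence foresees Cox models, univariable and multivariable, without naming a covariate. Section {20a} also plans to compare patient characteristics between arms. Section {20b} then says that neither subgroup nor adjusted analyses are planned.

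**The concern.** Without randomisation, the comparison rests on the two groups being alike in prognosis. The article itself names a place where they may not be. Regimen is chosen patient by patient, it generally follows frailty and age, and the groups were treated in different years. If the trial enrolled fewer frail or elderly patients than the 2014–2018 cohort, its PFS would be longer with no contribution from PET. If it enrolled more, a real benefit would be masked.

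An unadjusted test cannot separate these explanations. The comparison of patient characteristics in {20a} would show an imbalance but would not correct the primary result. The multivariable Cox model could correct it, but {20b} rules adjustment out. As written, the plan leaves a known prognostic difference uncorrected.

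**Working it through.** **The plan's own figure.** Inputs from {14}: hazard ratio 1.65, 5% significance (taken as two-sided), 80% power.
- Schoenfeld: 4 × (1.96 + 0.8416)² / (ln 1.65)² = 4 × 7.849 / 0.2508 = 125.2, so 126 events in total, or 63 per arm.
- Freedman: (2.65 / 0.65)² × 7.849 = 130.5, so 131 in total, or 65.5 per arm.

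The stated 65 events reproduces as a per-arm count. What matters here is that the calculation has no term for a difference in case mix.

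**How regimen mix alone moves the median.** The article gives neither regimen shares nor regimen-specific PFS, so what follows is assumed. Let the shorter-course share be p0 in the historical cohort and p1 in the trial. Let PFS be exponential with hazard λ under the longer course and hλ under the shorter. Fix the historical median at 4.9 months:

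(1 − p0)·exp(−4.9λ) + p0·exp(−4.9hλ) = 0.5

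Take h = 2, p0 = 50%, p1 = 20%.
- With x = exp(−4.9λ), the equation becomes x + x² = 1. Then x = 0.618 and λ = 0.4812 / 4.9 = 0.0982.
- The trial median solves 0.8y + 0.2y² = 0.5, giving y = 0.5495 and t = 0.5987 / 0.0982 = 6.10 months.

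So the median rises from 4.9 to 6.10 months with no PET effect. The design target is 8 months.

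**Effect on the test.** Simulations with no PET effect used 44 historical and 67 trial patients, 38 months' accrual plus 6 months' follow-up, and an unadjusted log-rank test. The table gives the rate of significance favouring PET (nominal 2.5%). Ranges show separate simulation runs.

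| Shorter-course share, historical vs trial | h = 1.5 | h = 2.0 |
|---|---|---|
| 30% vs 30% | 2.5–2.8% | 2.5–3.0% |
| 40% vs 20% | 6.4–6.5% | 8.5–10.0% |
| 50% vs 20% | 8.9–9.4% | 15.1–15.8% |
| 20% vs 40% | 1.2–1.3% | 0.6–0.7% |

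More extreme assumptions give more (50% vs 10% with h = 2.5: about 32%), but nothing in the article points to them.

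**Would stratifying by regimen repair it?** That depends on why the mix differs.
1. *Regimen is the only prognostic factor.* Stratified rates are about 2.5–3.2%. This follows from the model's construction.
2. *Frailty is the same in both arms, but the threshold for the shorter course moved.* With shares of 20% vs 40%, the unstratified test stays at 2.9%, while the stratified test rises to 6.2% (mean-hazard ratio between regimens about 1.5) or 8.8% (about 2.0). With 20% vs 50% it gives 8.6% and 13.3%. With 40% vs 20% it falls to 0.6–1.0%.
3. *Frailty itself is lower in the trial arm.* Unstratified rates of roughly 12–33%, depending on the assumed shift, fall only to about 6–9% when stratified.

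Cases 2 and 3 were checked by a fresh simulation with a continuous frailty scale. It gave rates close to those in case 2 and the same pattern in case 3: a large inflation that stratifying by regimen only partly removes.

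**The case against.** The strongest case against is that the size is assumed throughout and the sign is unknown. That stands. The table shows what could happen, not what did. Even 60% vs 10% with a regimen hazard ratio of 2.5 gives an apparent hazard ratio of about 1.51, below the design value of 1.65.

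It can also be said that a condensed article need not tabulate the historical regimen mix or list covariates. That stands too, and the missing split is not held against the plan. But {20b} goes further than leaving detail to another document: it states that adjustment is not planned, against {20a}.

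Two stronger readings are tempting.
- A reader might infer that physicians choose the regimen in response to PET, since Tables 1 and 2 place PET in screening before chemoradiotherapy and the trial is open-label. No passage says that PET extent informs the regimen; the factors named are frailty and age. The possibility is not excluded, which is a reason for caution in adjusting for the regimen given, but it is not a documented defect.
- A reader might infer that a regimen-stratified test settles the matter. It does so only if regimen carries all of the prognosis. The article instead describes regimen as a discretionary marker of frailty, and under that description stratification can leave bias or create it.

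**Conclusion.** The point holds in this form. A nonrandomised, confirmatory PFS comparison pools two regimens whose choice generally follows frailty and age, tests them unadjusted, and contradicts itself on whether adjustment will be made. A case-mix difference between 2014–2018 and the trial can therefore be mistaken for a PET effect or hide one.

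The unadjusted false-positive rate favouring PET runs from below 1% to about 15%, against 2.5% nominal. This rests on assumed shorter-course shares of 20–50%, regimen hazard ratios of 1.5–2.0, exponential PFS and a two-sided 5% test. A shift in underlying frailty could take it higher. The documents do not show that any imbalance exists or which way it runs. The plan should be changed on this point because correction is cheap and the comparison has no other protection against case mix.

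**What to change.** 1. Reconcile {20a} with {20b}, so that the plan states once whether the primary comparison is adjusted.
2. Prespecify, before the arms are compared, a Cox model for PFS with arm, age and ECOG performance status as the primary comparison. Age is collected under {18a}, and ECOG is recorded at screening in Tables 1 and 2. Their availability for the historical cohort is an assumption to confirm.
3. Tabulate regimen, age and ECOG by arm.
4. Report a regimen-stratified log-rank test and Cox model as a sensitivity analysis, not as the only correction. Thresholds may have drifted between periods, and treatment starts after PET with nothing fixing the choice earlier.

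Recording the intended regimen before PET would come too late as a main remedy: {9} planned recruitment to end in February 2024, and the article appeared in June 2024.

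The cost is some analysis work and a few degrees of freedom. With a trial median of 8 months, the event probability over 38 + 6 months is about 0.83, so 67 patients give about 55 events. With 44 historical events (assuming all progressed or died) that makes about 99. Arm, age and ECOG (0–2) use four parameters, or about 25 events each. Measured age and ECOG will not remove every difference between periods. The physician's choice of regimen stays as it is.

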### Outcomes {12}

Primary Outcome Measures of the clinical trial are to demonstrate the progression-free survival (PFS) in the 11C-methionine PET/CT arm as Experimental arm vs. PFS in the historical patient cohort as an arm Ahist. PFS was defined as the time from the start of radiotherapy to the progression of disease or death [Time Frame: 44 months].

The secondary outcomes are the following:

Rapid-Early-Progression incidence [Time Frame: 38 months]Prospective evaluation of the incidence of Rapid-Early-Progression (REP) on planning MR in patients with GBM indicated for adjuvant chemoradiotherapy.Overall survival (OS) in the Experimental Arm vs. Arm Ahist [Time Frame: 44 months]OS in the Experimental Arm compared to the historical retrospective group (arm Ahist). OS = time from surgery to death related to glioblastoma multiforme.Biomarkers I [Time Frame: 38 months].Immunohistochemical analysis of GFAP, Ki-67, IDH1, ATRX, and PDL1. GFAP: positive/negative/focal positive Ki-67, IDH1: positive/negative, ATRX loss of expression: positive/negative, PDL1 protein expression: positive/negative.Biomarker II [Time Frame: 38 months]Mutational status of TERT and IDH2: mutated/wild-type.Biomarkers III [Time Frame: 38 months]Sanger sequencing of IDH1 in IDH1 IHC-positive patients: mutated/wild-type.Biomarkers IV [Time Frame: 38 months]MGMT promoter methylation status: ≥ 25% = methylated/ < 25% = unmethylated.Biomarkers V [Time Frame: 38 months]1 p/19 q codeletion: positive/negativePattern-of-failure analysis [Time Frame: 44 months]Evaluation of spatial patterns of failure (PoF; central (V95% ≥ 95%)/in-field (80% ≤ V95%)/marginal (20% ≤ V95% < 80%)/distant (V95% < 20%)) in patients with REP (the Experimental Arm) compared to the historical retrospective group (Arm Ahist). In the case of multifocal progression, each PD is evaluated independently, i.e., the patient could have one central and one distal PD. In subsequent statistical analysis, each PD was evaluated independently. PoF could be performed even in deceased subjects if MR describing the progression is available.Quality of Life assessment using the standardized European Organization for Research and Treatment of Cancer (EORTC) questionnaire QLQ-C30 [Time Frame: 44 months]Quality of life will be assessed using a standardized questionnaire: the European Organization for Research and Treatment of Cancer Quality of Life Questionnaire C30 v.3.0 during the screening period, visits 2, 4, 6, 8, 10, and 12 (End-Of-Treatment) and during the follow-up period every 3 months (± 1 week) up to progression of the disease.Quality of Life assessment using the standardized European Organization for Research and Treatment of Cancer (EORTC) Quality of Life questionnaire-BN20 [Time Frame: 44 months]Quality of life will be assessed using a standardized questionnaire: additional module Brain Cancer European Organization for Research and Treatment of Cancer Quality of Life questionnaire BN20 during the screening period, visits 2, 4, 6, 8, 10, and 12 (End-Of-Treatment) and during the follow-up period every 3 months (+/- 1 week) up to the disease.

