
### Participant timeline {13}

The schedule of enrolment, intervention and visits is summarized in Tables 1 and 2. The duration of the study participation is 44 months (recruitment 38 months + 6 months follow-up).

**Table 1 Tab1:** Participant timeline for the regimen according to Stupp

4.3.1.Stupp regimen	Screening	CHEMO RADIO THERAPY	Visit 1	Visit 2	Visit 3	Visit 4	Visit 5	Visit 6	Visit 7	Visit 8	Visit 9	Visit 10	Visit 11	Visit 12 (EoT)	Follow-up until PD	EoS Visit
Days / Months	**max. 14 D**	**D1-D42** **(M 1–2)**	**D42 + 1 M** (± 1 tweek)	** + 1 M**	** + 1 M**	** + 1 M**	** + 1 M**	** + 1 M**	** + 1 M**	** + 1 M**	** + 1 M**	** + 1 M**	** + 1 M**	** + 1 M**	**Every 3 M** (± 1 tweek)	**PD**
Inclusion/exclusion criteria	X															
Informed consent	X															
Anamnesis^a^	X															
Pregnancy test (serum/urine)	x*	xx*	x	x	x	x	X	x	x	x	x	x	x			
HIV, HBV, HCV test	X**															
Physical and laboratory examination^b^	X**	x***	x	x	x	x	x	x	x	x	x	x	x	x		
ECOG Performance status	X	x	x	x	x	x	x	x	x	x	x	x	x	x		
Extent of surgery^c^	x															
^11^C-MET PET/CT^d^	x															
Quality of life questionnaires^e^	x			x		x		x		x		x		x	x	
MR and RANO evaluation^f^				x (á 3 months)												
Molecular markers^g^	*To be performed during the patient's participation in the study*															
Radiotherapy **(start max. 8 weeks since surgery and max. 2 weeks after planning MR)**		x														
Chemotherapy **(start max. 8 weeks since surgery and max. 2 weeks after planning MR)**		x	x	x	x	x	x	X	x	x	x	x	x	x		
Adverse events		x	x	x	x	x	x	X	x	x	x	x	x	x	x	x
PoF analysis^h^																x

The description of performed examinations:

^*^The pregnancy test will be performed at the center (1. As part of the screening phase before 11C-methionine applications and 2. Before the 1st application of concomitant chemoradiotherapy)

^**^Laboratory analysis incl. tests for HIV, HBV and HCV will be performed in the screening phase if they have not been performed in the previous 5 days

^***^Laboratory analysis (blood count + differential + biochemistry) will be performed every week as part of CHRT. Physical examination will be performed on D1 and D21 (if not performed in the previous 5 days)

^a^Anamnesis

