### Plans to promote participant retention and complete follow-up {18b}

The study site will make every reasonable effort to follow the participant for the entire study period. Study site staff members will be responsible for developing and implementing local standard operating procedures to achieve maximal follow-up.

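### Overall survival is defined by glioblastoma-related death only, so it is cause-specific survival under the wrong name and does not match the any-cause death counted in PFS

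*Protocol article*

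**What the plan says.** Outcomes {12} lists OS as a comparison of the Experimental Arm with the historical arm Ahist over 44 months and defines it as "OS = time from surgery to death related to glioblastoma multiforme". Statistical methods for primary and secondary outcomes {20a} carries the same restriction, in brackets: "OS is considered the time from surgery to death (in relation to GBM".

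PFS has no such restriction. Outcomes {12}: "PFS was defined as the time from the start of radiotherapy to the progression of disease or death". Statistical methods {20a}: "PFS is considered the time from the start of radiotherapy to the occurrence of progression or death".

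The trial is open-label (Blinding {17a}), and the comparator is a historical cohort collected in 2014–2018 (Explanation for choice of comparator {6b}), with 44 patients (Sample size {14}).

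In Participant timeline {13}, the last columns of Tables 1 and 2 are "Follow-up until PD", every 3 months, and an end-of-study visit timed at PD. No later contact is shown. The same section gives 44 months of participation (38 of recruitment plus 6 of follow-up). The retention section {18b} adds: "The study site will make every reasonable effort to follow the participant for the entire study period". Data management {19} names medical records as a data source.

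**The concern.** An endpoint called overall survival will be read as death from any cause. Here a death judged unrelated to glioblastoma is not an event. This has three consequences.

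- **The two survival endpoints disagree.** A patient who dies without progression, of a cause judged unrelated, has a PFS event but no OS event.
- **The event depends on a judgement.** Death from any cause needs none. Relatedness does, and it has to be judged for patients whose treatment is known and, in the other arm, for a cohort assembled retrospectively. Any difference in how readily deaths are called unrelated feeds straight into the OS hazard ratio.
- **The reported median is not comparable** with OS medians elsewhere, because removing deaths lengthens it.

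A smaller, separate matter is that the visit tables end each patient's study at progression while OS runs on a 44-month time frame. The document does not connect the two.

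**Working it through.** **1. No plan figure to reproduce.** The document states no OS event count, effect size or power. Sample size {14} concerns PFS only and does not depend on the OS definition.

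**2. The definitions side by side.**

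| Patient | PFS | OS as written |
|---|---|---|
| Progresses, then dies of glioblastoma | event at progression | event at death |
| Dies without progression, judged related | event at death | event at death |
| Dies without progression, judged unrelated | event at death | no event |
| Progresses, then dies, judged unrelated | event at progression | no event |

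The last two rows would be OS events under the usual definition.

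**3. Effect on the hazard ratio.** Let f be the share of deaths judged unrelated, taken as constant over time. The hazard of a counted death is then (1 − f) times the all-cause hazard, so

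apparent HR (experimental/historical) = true HR × (1 − f_exp)/(1 − f_hist).

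The document gives no value of f; the shares below are assumptions. The true HR is 1.0.

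| f_exp | f_hist | Apparent HR |
|---|---|---|
| 5% | 0% | 0.95 |
| 10% | 0% | 0.90 |
| 0% | 5% | 1/0.95 = 1.05 |
| 0% | 10% | 1/0.90 = 1.11 |
| 10% | 5% | 0.90/0.95 = 0.95 |
| 5% | 10% | 0.95/0.90 = 1.06 |
| 10% | 10% | 1.00 |

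A wider contrast of 2% against 15% gives 0.98/0.85 = 1.15, or 0.85/0.98 = 0.87 the other way round.

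**4. Effect on the median.** With exponential survival, apparent median = true median/(1 − f). The document gives no OS median for patients with rapid early progression. Taking the 14.6 months that the Introduction quotes for radiotherapy plus temozolomide, purely as an illustration:

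- f = 5%: 14.6/0.95 = 15.4 months
- f = 10%: 14.6/0.90 = 16.2 months

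This occurs even when the shares are equal and the hazard ratio is undisturbed.

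**5. How many deaths.** Inputs from Sample size {14}: 67 patients, uniform accrual over R = 38 months, then 6 months of follow-up. Assumptions: exponential OS with median 10–17 months, and 1.4 months from surgery to radiotherapy, so F = 7.4 months.

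P(death by month 44) = 1 − [exp(−λF) − exp(−λ(R + F))]/(λR), with λ = ln 2/median.

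- Median 10: 67 × 0.79 = 52.9 deaths
- Median 17: 67 × 0.62 = 41.8 deaths

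With f = 5–10%, about 2 (41.8 × 0.05 = 2.1) to 5 (52.9 × 0.10 = 5.3) trial-arm deaths would not count.

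**6. The visit tables against the OS time frame.** With a PFS median of 8 months (Sample size {14}), the same formula with F = 6 gives 67 × 0.826 = 55.3 PFS events. If 5–20% of these are deaths without progression (an assumption), 55.3 × 0.05 = 2.8 to 55.3 × 0.20 = 11.1 deaths fall within the scheduled visits. The remaining deaths follow progression and must be learned of outside the schedule. This shows why the source needs stating; it does not show that the deaths will be missed.

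**The case against.** The strongest case on the other side has four parts.

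**Follow-up.** A reader might infer from the tables that OS is censored at progression and therefore cannot be observed as planned. The document does not say that. The tables list visits, and a date of death needs no visit. Data are drawn from medical records, the site undertakes to follow patients for the whole study period, and OS has a 44-month time frame with no stop at progression. For the QLQ-C30, by contrast, the same section expressly ends collection at progression. The article also condenses a fuller protocol that may describe survival tracing. This objection stands: only the need to reconcile the tables with the time frame remains.

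**Treatment-related deaths.** A reader might also infer that deaths from toxicity or complications drop out of OS. The document does not say how these are classed, and a broad reading of relatedness could include them. Nor does it say who judges the cause. This stands too: what can be said is that the restriction is undefined and open to judgement.

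**Size.** The shares are assumed, the direction is unknown, and similar attribution in both arms leaves the hazard ratio near 1. This is correct.

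**Importance.** OS is one of several secondary outcomes with no stated power, and the primary endpoint already counts any death. This is correct and limits the weight of the point.

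None of this touches the definition. It is stated in two sections, so it is not a slip in one of them, and nothing elsewhere in the document corrects it.

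**Conclusion.** The definition of OS is wrong as written. It is cause-specific survival, it is inconsistent with PFS, and it brings a cause-of-death judgement into an open-label comparison with a retrospective cohort.

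The likely effect is modest and could go in either direction: a true hazard ratio of 1.0 appears as about 0.90–0.95 or 1.05–1.11 if 5–10% of deaths are excluded in one arm only. These figures rest on assumed shares that are constant over time. The lengthening of the median also assumes exponential survival.

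On follow-up, the conclusion is narrower: the tables show no contact after progression, and this has to be squared with the 44-month OS comparison. It does not follow that OS is censored at progression or cannot be observed.

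The point should be settled before the OS analysis. It does not alter the primary PFS analysis or the sample size.

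**What to change.** 1. In Outcomes {12} and Statistical methods {20a}, define OS as time from surgery to death from any cause, identically for both arms.
2. If glioblastoma-specific death is of interest, keep it at most as a supportive analysis under its own name, with other deaths treated as competing events and a stated rule for relatedness.
3. In Participant timeline {13}, add a sentence or table note that vital status after PD is taken from medical records in both arms, so that the end-of-study visit at PD and the 44-month OS time frame agree.

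The cost is a change of wording and a check of records at one centre. No visits, imaging or patients are added.
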